### 5.3.2 **Secondary study outcome 2 – Factors influencing applicability**

It will be assessed whether the following factors influence GAIA case definition applicability:

- Health facility level (primary, secondary, tertiary/referral)
- Region
- Qualification of research staff to identify cases and to complete CRFs
- Availability of technical equipment (e.g. laboratory, ultrasound, type of scale etc.)

The proportion of cases identified that can be classified across all sites will be tabulated and then stratified by the factors above. A Chi-square test will be used to assess whether there are any significant differences between the categories.

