## 4 Methodology

### 4.1 Study design

This will be a prospective observational study at selected sentinel sites, mostly in LMICs.

As this study is observational, no changes to routine clinical and diagnostic practice will take place, however data recording from routine clinical practice is expected to be more complete and data access easier than in a retrospective study. During a feasibility assessment it was found that, at the majority of sites, medical records are not available in electronic format and archives are not easily accessible. Sites also expressed concerns on the limitation of their medical records maintenance: data that had been generated might not be recorded or might not be retrieved. Hence a prospective study design is proposed to ease access to quality data.

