### *Factors that potentially affect classification*

Information on factors that potentially affect classification were collected through a one-off questionnaire that will be completed once by each site. This will include questions on:

- Health facility level (primary, secondary, tertiary/referral)
- Health facility type (public, private)
- Qualification of staff to identify cases and to complete CRFs
- Availability of technical equipment (e.g. laboratory, ultrasound, type of scale etc.)
- Record keeping.

In addition, the questionnaire will contain a question on the gestational age cut-off that is considered non-viable live birth at each site/country (see section 4.6.3).

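### The factor analysis in 5.3.2 omits record keeping and facility type, which 4.8 collects for that purpose, so a record-keeping effect on the seven health outcomes could be credited to equipment or facility level

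*Protocol*

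**What the plan says.** Section 4.8, under its heading on factors that may affect classification, describes the source: "Information on factors that potentially affect classification were collected through a one-off questionnaire that will be completed once by each site". It lists five factors: facility level, facility type (public or private), staff qualification, technical equipment, and "Record keeping".

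Section 5.3.2, which serves the second secondary objective, opens with "It will be assessed whether the following factors influence GAIA case definition applicability" and lists four: facility level, region, "Qualification of research staff to identify cases and to complete CRFs", and technical equipment. The proportion of identified cases that can be classified is tabulated over all sites, then stratified by those factors, with a chi-square test between categories. No joint or adjusted analysis is stated.

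Elsewhere, 5.2.2.1 stratifies applicability for the health outcomes by site, country, region and facility level. Section 5.2.2.2 does the same for maternal immunisation and adds paper versus electronic data. In 4.1 the protocol reports that sites were worried about their records: "data that had been generated might not be recorded or might not be retrieved".

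**The concern.** A case can go unclassified for two different reasons: the measurement was never made, or it was made and cannot be found in the record. Equipment bears mainly on the first and record keeping on the second. The two may well go together across sites. If only equipment and facility level are tabulated, each one-way table absorbs whatever part of a record-keeping effect is correlated with it.

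The purpose of the objective is to learn which factors influence applicability, and section 9 says the gaps found should help in planning next steps. Record keeping is one of the few site weaknesses that the protocol itself documents, so its absence from the list for all seven health outcomes matters more than the loss of an arbitrary covariate.

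**Working it through.** **1. The two lists side by side**

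| Factor | Collected (4.8) | Analysed (5.3.2) |
|---|---|---|
| Facility level | yes | yes |
| Facility type (public/private) | yes | no |
| Staff qualification | yes | yes |
| Technical equipment | yes | yes |
| Record keeping | yes | no |
| Region | known by design | yes |

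Three of the five collected factors carry over, two drop out and one is added.

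**2. Is the gap filled elsewhere?**

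- Facility type appears in none of the strata in 5.2 or 5.3.
- Record type appears once, in 5.2.2.2, for maternal immunisation. It is absent from 5.2.2.1 and 5.3.1.1, which cover the health outcomes.
- Section 5.4 tabulates which required elements were missing. Some forms in Annex V separate an unmade measurement from an unrecorded one: ultrasound done and then its date and result; chest X-ray performed and then its finding; newborn weighed and then the weight. Others do not. Several signs on the bloodstream infection form offer a single answer covering both unknown and not measured, and the microcephaly form asks in one question whether head circumference was measured and recorded.

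**3. How large could the misattribution be?**

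The protocol has no figure to reproduce, so every input here is assumed. Suppose 80% of cases can be classified at sites with good records and 50% at sites with poor records, and equipment has no effect. If a share *a* of cases in an equipment group comes from sites with good records, the expected proportion classified is

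0.8a + 0.5(1 − a) = 0.5 + 0.3a,

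and the apparent equipment effect is 0.3 × (a₁ − a₂).

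| Good records: equipped / unequipped | Classified | Apparent effect | Chance that the test flags equipment, 300 cases per group | Same, 1000 per group |
|---|---|---|---|---|
| 60% / 40% | 68% v 62% | 6 points | about 34% | about 80% |
| 70% / 30% | 71% v 59% | 12 points | about 87% | nearly 100% |
| 90% / 20% | 77% v 56% | 21 points | nearly 100% | nearly 100% |

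The probabilities come from a two-sided 5% comparison of two proportions that treats cases as independent. Cases cluster within sites, so they are a rough guide only. Within a record-keeping stratum the apparent effect is zero by construction.

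**4. What could a joint table show?**

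Section 4.2 gives 25 sites and, by level, one primary, four secondary and eighteen tertiary. These add to 1 + 4 + 18 = 23, so two are unaccounted for. The factors vary by site, not by case. The one primary site can fall in only one record-keeping stratum, and four secondary sites leave almost nothing to compare. A table of equipment within record-keeping strata can describe a pattern but cannot firmly separate the two factors.

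**The case against.** The strongest reply is that the omission costs little. Four parts of it deserve weight.

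- **Section 5.4 gives case-level evidence.** Where a form asks in two steps whether something was done and what was found, it says more about measurement against recording than a once-per-site answer can. This stands, but only for those items.
- **The prospective design was chosen to ease the records problem.** Section 4.1 expects fuller recording and easier access, and 8.3 has sources mapped site by site beforehand. This also stands: 4.1 shows that record keeping was a concern, not that it will be the main confounder.
- **The number of sites and the one-way tests limit separation as much as the missing entries do.** This is right, and it restricts the remedy to description. It is not a reason to leave the factor out.
- **An analysis plan could add strata.** It could, but 5.3.2 does not defer the list; it states one that disagrees with 4.8.

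The case for facility type is weaker. The protocol suggests no mechanism for it, and the site descriptions in Annex II were not in the text available here, so it is unknown whether any site is private.

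A reader might infer that both factors go wholly unused, or that the study would end by recommending the wrong investment. The documents support neither. Paper versus electronic data is used for maternal immunisation, and no investment recommendation is planned.

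**Conclusion.** The point holds as a mismatch between two sections with a real, moderate consequence for one secondary objective. Two of the five factors collected for this purpose are missing from the analysis without explanation, and for the seven health outcomes no planned table uses record keeping. Equipment or facility level could therefore be credited with a record-keeping effect, and 5.4 corrects this only in part.

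The size is not known. The 6 to 21 points above depend entirely on assumed classification rates and on an assumed link between records and equipment; with no such link there is no distortion. Nor does the protocol say that these factors are expected to affect classification, only that they may. The primary objectives are not affected.

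**What to change.** - **Section 5.3.2:** add record keeping, using the questionnaire's own categories, and add facility type if both public and private sites take part. If either is left out on purpose, say why.
- **Section 5.2.2.1:** add the paper/electronic split already planned in 5.2.2.2. This measures the format of records, not their quality, so it does not replace the record-keeping factor.
- **Equipment table:** show it also within record-keeping strata, with the number of sites in each cell and no test, and state that about 25 mostly tertiary sites cannot firmly separate the factors.

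The questionnaire is not reproduced in the protocol and the forms in Annex V do not ask about record format. It should therefore be confirmed that the questionnaire, or the source mapping in 8.3, yields the paper/electronic distinction for each outcome. If so, no new data are needed.

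The cost is a few lines, a few tables, and additional unadjusted comparisons across seven outcomes, which should be labelled as such.

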### 4.2 Study setting

The study will be performed at 25 sites in seven LMICs (Ghana, South Africa, Tanzania, Zimbabwe, Iran, India, Nepal) and one high-income country (HIC) (Spain). The sites consist of one primary care centre, four secondary and eighteen tertiary hospitals with a maternity ward. Sites have been selected based on site selection criteria and acceptable performance in a simulation exercise that tested sites' actual minimum capacity in data collection (Annex 1).

The following sites will participate (country, city, site). Sites characteristics are further described in Annex 2:

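### Factors fixed per site are tested with a chi-square on pooled cases, which raises the false-positive rate by an amount that depends on between-site variation and cases per site

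*Protocol*

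**What the plan says.** Protocol section 5.3.2 sets out the analysis for secondary objective 2. The unit is the case: "The proportion of cases identified that can be classified across all sites will be tabulated and then stratified by the factors above". The test then follows: "A Chi-square test will be used to assess whether there are any significant differences between the categories". The factors are facility level, region, availability of technical equipment, and "Qualification of research staff to identify cases and to complete CRFs".

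Section 4.8, under the factors that may affect classification, says that the information on facility level, staff qualification and equipment is "collected through a one-off questionnaire that will be completed once by each site". Region is not on the questionnaire, but it is fixed by where the site lies.

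Section 4.2 gives the number of sites, "The study will be performed at 25 sites in seven LMICs" plus one high-income country, and their levels: "The sites consist of one primary care centre, four secondary and eighteen tertiary hospitals with a maternity ward". Section 5.1.2 aims for 100 cases per outcome per site and accepts that some outcomes and sites will fall short. Section 6 lists as a limitation that the feasibility of data collection is specific to the site. The protocol mentions no random site effect, robust variance, design effect or site-level analysis.

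**The concern.** A chi-square on pooled counts takes every case as an independent observation. Here the explanatory variable varies only between sites, so the comparison of categories is a comparison of groups of sites. Its error variance must include the variation between sites within a category, and the case-level chi-square leaves that component out. If sites differ in how often cases can be classified, for reasons unrelated to the factor, the test reads part of that difference as an effect of the factor.

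This is the only hypothesis test that the protocol names, and it supplies the inferential answer to secondary objective 2. It would be run for several factors and seven health outcomes. The study is meant to inform later vaccine safety studies, so a spurious effect of facility level, staffing or equipment could carry over into their planning.

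**Working it through.** **The plan's own figure.** Table 1 in section 5.1.2 uses n = z² p(1−p)/h². At p = 0.5 and h = 0.10 this is 1.96² × 0.25/0.01 = 96.04, rounded up to 97 as stated. The other cells reproduce too. The formula has no design effect and needs none, because it concerns precision within one site. It does not carry over to a comparison between groups of sites.

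**Inputs.**
- From the protocol: m up to 100 cases per outcome per site (5.1.2); facility-level split 1/4/18 (4.2).
- Assumed: two-sided 5% level (5.3.2 states none); applicability 50%, the worst case of Table 1; equal m at every site; a 12/13 split for a two-category factor; intra-site correlation (ICC) from 0 to 0.20, because the documents give none.

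**Formulas.** Design effect DE = 1 + (m − 1) × ICC. At p = 0.5 the between-site standard deviation is √(0.25 × ICC). For two categories with equal m, the actual level of the case-level test is about 2 × [1 − Φ(1.96/√DE)]. At ICC 0.05, DE = 1 + 99 × 0.05 = 5.95, 1.96/√5.95 = 0.80, and the level is 42%.

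The three-category factor was simulated: 20,000 datasets per setting with no factor effect, beta-distributed site proportions, binomial counts and a Pearson chi-square. The two-category factor was simulated in the same way as a check on the formula.

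Actual false-positive rate with 100 cases per site:

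| ICC (assumed) | Site SD, points | DE | Facility level 1/4/18 | Two categories 12/13 | Closed form, two categories |
|---|---|---|---|---|---|
| 0 | 0 | 1 | 5% | 5% | 5% |
| 0.01 | 5 | 1.99 | 22% | 16% | 16.5% |
| 0.02 | 7 | 2.98 | 36% | 25% | 25.6% |
| 0.05 | 11 | 5.95 | 61% | 42% | 42.2% |
| 0.10 | 16 | 10.9 | 78% | 55% | 55.3% |
| 0.20 | 22 | 20.8 | 89% | 67% | 66.7% |

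The result depends little on the assumed applicability: at ICC 0.05, facility level gives 61% at p = 0.8 and 60% at p = 0.9.

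Dependence on cases per site, at ICC 0.10:

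| Cases per site | Facility level 1/4/18 | Two categories 12/13 |
|---|---|---|
| 5 | 11.4% | 10.1% |
| 10 | 21.5% | 15.8% |
| 20 | 37.1% | 25.2% |
| 50 | 62.2% | 41.5% |
| 100 | 77.9% | 55.3% |

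**Check of the repair.** One-way analysis of variance on site proportions, with 100 cases per site and ICC 0.01 to 0.20, rejects in 3.4% to 5.1% of null datasets for the 1/4/18 split and in about 5% for the two-category splits.

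**The case against.** The strongest case against the point is about its size. The ICC is unknown; at zero the test is valid, and for rare outcomes with few cases per site the excess is modest. The calculations also assume no true effect, whereas the GAIA levels depend on scales and ultrasound, so some equipment effects may be real. Results are also reported by site (5.2.2.1, 5.3.1.1), which will make site variation visible. Neither primary objective uses this test. All of this stands and limits the weight of the point. It does not rescue the test: section 6 itself expects feasibility to be site-specific, and when an effect is real the case-level p-value still overstates the evidence for it. A separate analysis plan could add an adjustment, but the protocol has already named the method.

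A reader might infer more than the documents support:

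- *That two sites have no level to be analysed under, because 1 + 4 + 18 = 23 and not 25.* The questionnaire in section 4.8 asks every site for its level. The count in 4.2 is a separate, minor point to reconcile.
- *That the effective sample is simply the number of sites.* With 25 sites of 100 cases, it is 2,500/10.9 ≈ 229 at ICC 0.10 and 2,500/2.98 ≈ 839 at ICC 0.02. The number of sites limits the degrees of freedom; it equals the effective sample only as the ICC approaches 1.
- *That all cases at a site share the same scale, staff and records.* Only the questionnaire value is fixed. The birth-weight form in Annex V asks about the scale, with only its operating-procedure block marked for completion once per site, and ultrasound is recorded per pregnancy.
- *That every stratum needs a site-clustered interval.* None can be estimated for one primary-care site, and with 25 sites in eight countries, about three each, it would be unreliable by country. The protocol prescribes no interval method for these proportions.

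**Conclusion.** The point holds in a limited form. Section 5.3.2 fixes a case-level test for site-level factors without allowing for clustering, and that test does not keep its nominal level unless sites are alike. The excess may run from a few percentage points, with low ICC or few cases, to a false-positive rate above one half for facility level at 100 cases per site and an ICC of 0.05 or more. These sizes rest on an assumed 5% level, an assumed ICC range, equal cases per site and no true effect. They describe a raised risk and do not mean that any particular factor will be falsely declared influential.

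For primary care, level and site are fully confounded, because one centre is the whole category; no choice of test separates them. The matter should be fixed, but it concerns one secondary objective and leaves the primary objectives and the per-site precision of Table 1 untouched.

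**What to change.** In section 5.3.2, replace the case-level chi-square with one of two analyses, named in advance:

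- a test with the site as the unit, for example a permutation test on site proportions; or
- a mixed logistic model with a random site effect, or GEE clustered on site, with a small-sample correction.

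State the significance level. Report the single primary-care site descriptively and leave it out of the test, so that facility level is tested as secondary against tertiary. Keep the planned tabulations by factor and by site.

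No new data are needed and only analysis wording changes. The cost is lower power: with about 25 sites, and four in the secondary category, fewer factors will reach significance and only large differences between site groups will be detectable.

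Separately, reconcile the counts in section 4.2 so that the breakdown by level adds up to the stated number of sites.

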## **5.4 Exploratory study outcomes**

### **5.4.1 Missing elements to meet GAIA case definition**

To better understand why GAIA case definitions are not met, the type of data elements that are required by the GAIA case definition but that are missing will be described.

For each health outcome, the reasons why identified cases could not be classified will be tabulated (e.g. four identified cases of neonatal death could not be classified because date of death was unknown).

If feasible, reasons will be grouped, and proportions will be calculated.

### **5.4.2 Missing elements to reach a better level of diagnostic certainty**

To better understand why the highest levels of diagnostic certainty are not met, cases that are classifiable at the Lowest levels of diagnostic certainty (Level 3, 4), the type of data elements that are required to meet a better level of diagnostic certainty will be described.

For each health outcome, the reasons why Level 3 or 4 cases could not be classified as Level 1 or Level 2 will be tabulated.

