#### 3.3 Exploratory objectives

1. To assess which missing data elements are preventing identified cases from meeting the GAIA case definition lowest level of diagnostic certainty.
2. To assess which missing data elements are preventing classified cases from meeting a better level of diagnostic certainty.

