#### 4.10 Case classification

Identified cases and exposures will be classified using the Brighton Collaboration ABC tool (Automatic Brighton Classification) [20] according to the levels of diagnostic certainty present in the GAIA definitions (Level 1-3, and Level 4-5 when applicable).

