## **5.5 Handling of missing data**

Missing data will not be imputed, and the data will be analyzed as they are recorded in the eCRFs. Missing data will be tabulated and explored as described in the exploratory objectives.

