### **Low birth weight**

#### Level 1 of diagnostic certainty

Newborn infant weighed within 24 h of birth

AND

Use electronic scale which is graduated to 10 g

AND

Scale is calibrated at least once a year

AND

Scale placed on level, hard surface

AND

Scale tared to zero grams

AND

Weight recorded as <2500 g

OR

Birth weight recorded as <2500 g

AND

Birth weight assessed as per health care facility's standard operating procedure, which fulfills criteria 1 to 5 of LOC1

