#### Level 2 of diagnostic certainty

Newborn infant weighed within 24 h of birth

AND

Scale (electronic/spring) is graduated to at least 50 g

AND

Scale is calibrated at least once a year, or more often if moved

AND

Scale tared to zero grams or 0.00 kg

AND

Weight recorded as <2500 g

OR

Birth weight recorded as <2500 g

AND

Birth weight assessed as per health care facility's standard operating procedure, which fulfills criteria 1 to 4 of LOC2

Scale used: could be electronic or spring scale, including color-coded scale.

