### Level 2A

1. Certain LMP\* with 2nd trimester scan (14 0/7 weeks to 27 6/7 weeks). If LMP and U/S do not correlate, default to U/S GA assessment.

OR

2. Certain LMP\* with 1st trimester physical examination.

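### Section 5.4.2 leaves Level 2 cases out of the missing-element table, although exploratory objective 2 covers every classified case that falls short of a better level

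*Protocol*

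**What the plan says.** Protocol section 3.3 states exploratory objective 2 as "To assess which missing data elements are preventing classified cases from meeting a better level of diagnostic certainty". The only condition is that the case is classified.

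Section 5.4.2 is the analysis for that objective. Its first paragraph gives the purpose as understanding why the highest levels are not met. It restricts attention to cases at Levels 3 and 4 and promises to describe the elements they would need for a better level. Its second paragraph fixes the table: "For each health outcome, the reasons why Level 3 or 4 cases could not be classified as Level 1 or Level 2 will be tabulated".

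Section 5.5 relies on the same objectives for missing data generally: "Missing data will be tabulated and explored as described in the exploratory objectives".

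Section 4.10 classifies cases at Levels 1 to 3, and at Levels 4 and 5 where a definition has them. A Level 2 case is therefore a classified case.

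**The concern.** The objective and its analysis do not cover the same cases. A Level 2 case is classified and has one better level above it, so it falls within objective 2, but section 5.4.2 does not admit it. If the plan is followed as written, the report will not say, for any of the seven outcomes, what kept Level 2 cases from Level 1.

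That information bears on the study's purpose. The Rationale (section 2.1) says the definitions are being assessed to inform future vaccine safety studies, and that some criteria may exceed a site's clinical capacity. What separates Level 2 from Level 1 is often a matter of capacity. For preterm birth it is a first-trimester scan. For low birth weight, Level 1 requires "Use electronic scale which is graduated to 10 g", while Level 2 accepts "Scale (electronic/spring) is graduated to at least 50 g".

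**Working it through.** No arithmetic applies to the contradiction itself. The check sets the scope of the objective beside the scope of the analysis, one upward step at a time.

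**Inputs.** Objective 2 (section 3.3); both paragraphs of section 5.4.2; the levels in Annex III. Annex III gives a Level 2 to all seven health outcomes (as 2A and 2B for congenital microcephaly, preterm birth and small for gestational age). It gives a Level 4 to four of them: congenital microcephaly, low birth weight, small for gestational age and stillbirth. Level 5 for small for gestational age means no evidence of the condition, so it adds no step.

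| Step to a better level | Within objective 2 | Described (5.4.2, first paragraph) | Tabulated (5.4.2, second paragraph) | Outcomes where possible |
|---|---|---|---|---|
| 2 to 1 | yes | no | no | 7 |
| 3 to 2 | yes | yes | yes | 7 |
| 3 to 1 | yes | yes | yes | 7 |
| 4 to 3 | yes | yes | no | 4 |
| 4 to 2 | yes | yes | yes | 4 |
| 4 to 1 | yes | yes | yes | 4 |

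Six steps fall under the objective and four are tabulated, so 6 − 4 = 2 are not. The step from 2 to 1 is neither described nor tabulated. The step from 4 to 3 is described but not tabulated.

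**Does another section fill the gap?**

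- Section 5.3.1 gives the number and proportion of cases at each level, without reasons.
- Section 5.3.2 tests factors for a case being classified at all, not for the level it reached.
- Section 5.4.1 covers only identified cases that could not be classified.
- Section 5.5 points back to the exploratory objectives and adds no table.

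None of them gives reasons for Level 2 cases.

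**What would a Level 2 row contain?** Annex III shows two kinds of shortfall.

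- *Element absent.* A preterm birth at Level 2 lacks a usable first-trimester scan.
- *Element recorded but criterion not fulfilled.* A bloodstream infection may be at Level 2 after samples were tested and no pathogen was found. A low birth weight case may be at Level 2 because the scale is known to be coarser than 10 g. Microcephaly Levels 1 and 2A differ only in when the head was measured. A small-for-gestational-age case can have a first-trimester ultrasound and still be at Level 2A because of the scale.

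The case report forms in Annex V record these items: first-trimester ultrasound, scale type and graduation, timing of head measurement, and samples tested with their results.

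**Size.** The number of cases left out is the number at Level 2. The Protocol states no expected distribution of levels, so no figure follows. Assuming a Level 2 share would only return that share.

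**The case against.** The restriction may be deliberate. Section 5.4.2 contrasts the lowest levels with Levels 1 and 2 taken together, and concentrating on the weakest cases suits a study worried about limited clinical capacity. Narrowing a one-line exploratory objective in the methods section is ordinary practice. That explains the choice but does not reconcile the texts: objective 2 has no such limit, and Annex III, for preterm birth, labels Level 1 alone as the highest level. A statistical analysis plan, which was not available here, could widen the table, but the Protocol itself fixes which cases enter it.

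Several stronger readings are tempting, and the Protocol does not support them:

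- *Level 1 requirements disappear from the report.* They do not. A Level 3 or 4 case is tabulated for missing Level 1 or Level 2, so an absent first-trimester scan can still appear. What is lost is the contribution of Level 2 cases.
- *The step from Level 4 to Level 3 is ignored.* The first paragraph of 5.4.2 covers it in words; only the table omits it.
- *Every Level 2 case has missing data.* Some have complete data and simply do not meet a Level 1 criterion, as shown above.
- *Leaving out Level 2 biases the analysis by selecting on the outcome.* This is a descriptive list of reasons, with no estimate or test. Conditioning on level is natural there.
- *Level 2 must be common because most facilities are tertiary.* Facility level says nothing about the distribution of levels; well-equipped sites might equally reach Level 1.

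The practical loss is also softened because section 5.3.1 will show how many cases are at Level 2 by site and facility level, and section 4.8 collects equipment availability once per site. Neither supplies case-level reasons.

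**Conclusion.** The point holds as a mismatch of scope. Objective 2 covers every classified case below Level 1, while section 5.4.2 covers only Levels 3 and 4. Reasons for not reaching Level 1 go unreported for Level 2 cases in all seven outcomes, and the step from Level 4 to Level 3 is missing from the table in four. The consequence is small: one exploratory, descriptive table answers a narrower question than the one stated. The number of cases concerned is unknown. The conclusion rests on reading a better level in objective 2 as any level above the case's own, which is its plain meaning.

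**What to change.** Reword section 5.4.2 along these lines: for each health outcome, and by current level, tabulate for every classified case below Level 1 (Levels 2, 3 and 4) the criteria not met for the next better level and those not met for Level 1. Show data that are missing or not recorded separately from criteria recorded but not fulfilled, such as a negative pathogen test, the scale's graduation or the timing of a measurement. Without that split, Level 2 rows would present complete records as data gaps.

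The cost is a rewritten sentence and a few extra table rows, using data already on the case report forms.

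If the sponsor does want only Levels 3 and 4, objective 2 should be limited to them. That also removes the contradiction, but gives up the Level 2 information.
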